**Implementation outcomes**				
Acceptability (Aim 7)	Interviews	Selected leaders	6 months post-training	Qualitative data will be analysed thematically [59] to understand perceptions of acceptability, variation in this, and factors impacting it.
Adoption (Aim 7)	Study specific questionnaire	Clinicians	6 months post-training	At each site the proportion of respondents reporting utilisation of each of the key resources will be calculated.
	Study specific questionnaire	Leaders	3 months post-training	For each site, the reported completion of each of the leader components will be calculated.
	Interviews	Selected leaders	6 months post-training	Qualitative data will be analysed thematically [59] to understand the extent of implementation undertaken and factors impacting this.
Appropriateness (Aim 7)	Interviews	Selected leaders	6 months post-training	Qualitative data will be analysed thematically [59] to understand perceptions of the appropriateness of the intervention, and any adaptations made.
Feasibility (Aim 7)	Interviews	Selected leaders	6 months post-training	Qualitative data will be analysed thematically [59] to understand perceptions of the feasibility of implementing MOHMQuit and the extent to which it has been integrated into usual care.
Fidelity (of delivery of the MOHMQuit intervention to the services) (Aim 7)	Training logs Researcher notes	Research team	Throughout	Data will be analysed to determine the proportion of eligible clinicians and leaders participating in training; the extent to which the training and other strategies were delivered as intended.
Context	Multiple	Internet, Partner Investigators and Leaders	Throughout	Information on service size, capacity, structure will be collated. Information from Partner Investigators and leaders regarding factors impacting delivery will be documented throughout the study period.
**Economic evaluation**				
Cost-effectiveness—the incremental cost per additional quitter from a service-provider perspective (Aim 6)	Within-trial data collection	Data will be sourced from study and site records as well as the existing literature.	Data collection throughout the study, with analysis at the end.	Economic evaluation conducted from the perspective of the Australian health care system with 8-month time horizon for cost-effectiveness and lifetime time horizon for cost utility. Probabilistic sensitivity analysis and non-parametric bootstrapping will be used to assess robustness of the model.
Cost-utility—lifetime analysis of the incremental cost per Quality adjusted life year (QALY) gained (Aim 6)	Modelled economic evaluation	Data will be sourced from study and site records as well as the existing literature.	Data collection throughout the study, with analysis at the end.	

*Key: NSW* New South Wales, *NSW Quitline* A state-based telephone Quitline service, *SCS* smoking cessation support, *eMaternity* the electronic health record used by maternity services in NSW.

^a^Study specific interview with postpartum women: women will be interviewed by a research midwife by telephone within 2 weeks of giving birth and asked about their smoking status in the final 7 days of their pregnancy. They will also be asked their perspectives of SCS provided in antenatal care using a structured interview schedule.

^b^Data extractions from eMaternity: deidentified, quantitative data will be extracted from the eMaternity database throughout the 32-month data collection period to analyse clinicians’ provision of best-practice SCS as documented in electronic-medical records (aim 2).

**Fig. 3 Fig3:**
[figure not shown]
MOHMQuit data sources and outcomes

#### Primary outcome (health outcome)

A 7-day point prevalence abstinence is an established abstinence outcome and can be combined with biochemical verification [56, 60]. For women who report at least 7 days of abstinence at the end of their pregnancy, and continued abstinence since, home-visiting midwives will collect saliva samples which will be tested for cotinine levels at a central pathology facility. The samples will be tested using liquid chromatography with tandem mass-spectrometry and a cut-point of 8 μg/L. A 7-day point prevalence abstinence with biochemical verification is commonly used in pregnancy smoking cessation trials, as longer timeframes (e.g. 12-month abstinence) are not relevant to benefits to the foetus [61, 62]. As biochemical verification will not always be possible, self-reported 7-day point prevalence (regardless of verification) will be used as a secondary outcome.

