Evidence-based Australian guidelines [14, 18] recommend routine SCS be delivered during antenatal care for all pregnant women using brief interventions based on the 5As (Ask, Advise, Assess, Assist and Arrange follow-up) and include providing nicotine replacement therapy (NRT) if women are otherwise unable to quit. However, provision of recommended SCS to pregnant women has remained persistently poor [19–21]. A state-wide survey of women’s experiences of maternity care in New South Wales (NSW) found that only 46% of women who smoked in pregnancy recalled being told about quitting programs [22]. Midwives, obstetricians and managers all reported major gaps in care, particularly in assisting women with cessation strategies and arranging follow-up [23, 24], both of which are crucial to quitting success [25, 26]. Despite the availability of guidelines and training, maternity care services have faced considerable barriers in implementing SCS [23, 27] illustrating the persistence of an evidence to practice gap. One possible reason for the gap has been lack of comprehensive and theoretically informed interventions to support services in delivering SCS, suggesting a theoretically underpinned systems change approach to guideline implementation is needed [28, 29].

Systems change interventions in public health services have been shown to be effective in increasing identification of smokers by clinicians and documentation of smoking status in electronic medical records, improving integration of SCS into usual care, and increasing the numbers of referrals to telephone Quitline services [30–32]. However, to date, only one adequately powered trial has tested the effectiveness of theoretically informed implementation strategies in antenatal settings [33].

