### Study design

The study is being undertaken as a partnership between academic researchers, policy makers within NSW State Government and non-government agencies and senior clinicians from participating sites. At each site, there is a Midwifery Partner Investigator and an Obstetric Partner Investigator supporting implementation of the trial.

The MOHMQuit trial is a pragmatic stepped-wedge cluster-randomised controlled trial of an implementation intervention in nine public maternity services in NSW. Our overarching goal is to increase smoking cessation among pregnant women to improve health outcomes. This trial will test the effectiveness and cost-effectiveness of the MOHMQuit intervention in achieving this, while also testing the mechanisms of action of the strategies based on the underpinning theoretical development of MOHMQuit. The specific aims of the trial are to compare the effectiveness of MOHMQuit versus usual care in increasing:Smoking cessation among pregnant women attending public antenatal services in NSW;The provision of guideline-recommended SCS as documented in *e*Maternity;Participating clinicians’ self-reported provision of guideline-recommended SCS to pregnant women;Participating clinicians’ knowledge, skills, confidence and positive attitudes regarding providing guideline-recommended SCS to pregnant women; andWomen’s reported receipt of cessation advice, resources and referral to quit smoking services.

Additional aims include the following:6.Determining the cost-effectiveness of the intervention in increasing smoking cessation;7.Assessing implementation of the intervention through a detailed process evaluation;8.Examining the mechanisms of action of the intervention strategies and moderators of their impact.

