#### Pregnant and postpartum women

A two-stage recruitment and consent process will be used to recruit pregnant and postpartum women to the study. In an initial opt-out process, all pregnant women presenting for antenatal care at the services will receive a PIS and be given the option of opting out of the study by contacting a research midwife by text. For women who remain and meet the eligibility criteria, a research midwife will contact them by text and then a telephone call, give a verbal explanation of the study, encourage women to ask any questions, and ask women to provide verbal consent to participating in a brief telephone interview. Women who consent to the telephone interview, and who report smoking abstinence in the 7 days before the birth of their baby, and since giving birth, will also be asked to consent to giving a saliva sample for cotinine testing. Importantly, all women will receive full ante- and postpartum care regardless of whether they consent to participate in the study.

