**Primary health outcome**				
Biochemically verified 7-day point prevalence abstinence at the end of pregnancy among pregnant smokers and recent quitters, confirmed by salivary cotinine testing. (Aim 1)	Structured telephone interview^a^ and salivary cotinine testing	Postpartum women	Within 2 weeks after giving birth	• The primary analysis will compare the odds of quitting smoking (cotinine-confirmed 7-day point prevalence abstinence) after the adoption of the intervention relative to the baseline rate. • To achieve this, logistic regression will be used within a generalised linear mixed model framework. • In addition to the fixed effect for intervention, a fixed effect for time will be included to adjust for any secular trends in the outcome. Random effects for site and time within site will be included to account for clustering by site and repeated measures over time. • Women who do not complete the biochemical verification will be classified as continuing smokers, as recommended in analyses of smoking cessation trials (e.g., see [56]).

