**Intervention outcomes**				
Documented provision of smoking cessation support (SCS) at booking visit and any subsequent visits. Offer of: • referral to a smoking cessation service including NSW Quitline • behavioural support • nicotine replacement therapy (Aim 2)	Deidentified data extraction of specified variables for all births to eligible women at intervention sites	*e*Maternity^b^	Throughout the 32-month collection period	• *e*Maternity SCS scores will be calculated based on the documented provision of SCS in *e*Maternity for each woman at each visit. • Scores will be modelled using a linear mixed model. Fixed effects will be included for time, intervention, and the interaction of these. •Random effects for site and participant will be included to account for clustering by site, and repeated measures on participants. •The interaction term will directly compare the rate of change in SCS scores over antenatal visits between pre and post-intervention.
Self-reported: • Provision of Advice to quit smoking • Provision of Assistance to quit smoking • Provision of referral to a quit smoking service (e.g. NSW Quitline or local service). (Aim 3)	Study specific questionnaire	Clinicians	Before training and 6 months post-training	• The outcome measure will be a composite score of self-reported provision of SCS, calculated from the questionnaires completed by clinicians prior to training and at 6 months post-training. • Post-intervention clinician SCS scores will be modelled using a linear mixed model. Fixed effects will be included in the model for the pre-intervention SCS score and time. A random effect will be included for site to account for randomisation by cluster.
Women’s reported receipt of: • Advice on quitting • Referral to a quitting program • Written self-help materials (Aim 5)	Structured telephone interview^a^	Postpartum women	Within 2 weeks after giving birth	• Receipt of SCS reported by women will be modelled using logistic regression in a generalised linear mixed model framework. Fixed effects for time and intervention will be included in the model and a random effect for site will be used to account for randomisation by cluster.
**Mediators** (for more detail on the identified barrier, intervention types, behaviour change techniques and measures, see Additional file 1)				

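### Cotinine at one cut-point cannot tell smoking from nicotine replacement, so the primary effect may be attenuated if replacement use at the postpartum sample rises after MOHMQuit

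*Protocol article*

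**What the plan says.** The section on the primary outcome fixes the assay and the threshold: "The samples will be tested using liquid chromatography with tandem mass-spectrometry and a cut-point of" 8 μg/L. Saliva is requested from women "who report smoking abstinence in the 7 days before the birth of their baby, and since giving birth", so selection for verification is by abstinence from smoking, not from nicotine. Table 2 gives the timepoint as "Within 2 weeks after giving birth" and adds a rule for missing samples: "Women who do not complete the biochemical verification will be classified as continuing smokers".

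On the care being promoted, the Background says that the Australian guidelines "include providing nicotine replacement therapy (NRT) if women are otherwise unable to quit". Under Study design, one aim is to increase clinicians' "self-reported provision of guideline-recommended SCS to pregnant women", and another is to increase the same care as documented in eMaternity. Table 2 lists the documented offer of NRT among the Aim 2 outcomes. Self-reported abstinence without verification is a secondary outcome, analysed in the same way as the primary.

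**The concern.** Cotinine is formed from nicotine whatever its source. A single cotinine cut-point therefore measures recent nicotine exposure, while the outcome of interest is smoking. For most women the two agree. They part for a woman who has stopped smoking and is still using NRT when the saliva is taken: she is abstinent by the trial's own question but can lie above 8 μg/L.

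A constant error of this kind would matter little. The difficulty is that the intervention is meant to raise provision of the care that includes NRT. If it also raises use at the time of sampling, the error becomes more frequent after the intervention than before, and some of its success is recorded as failure. The Randomisation and blinding section relies on biochemical verification to reduce bias for the primary aim. For these women, verification could itself introduce an error related to phase.

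**Working it through.** **Inputs.** From the Primary hypothesis and Sample size sections: 16% at baseline, 21% after the intervention. From the Primary outcome section: one marker, one cut-point of 8 μg/L. Assumed, because the documents give no figure: f0 and f1, the shares of truly abstinent women whose cotinine lies above the cut-point because of NRT, before and after the intervention.

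**The plan's own figures.** 16% + 5 points = 21%. The relative risk is 21/16 = 1.31 and the odds ratio is (0.21/0.79)/(0.16/0.84) = 1.40. The Primary hypothesis states these as cotinine-confirmed rates.

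**Formula.** Leaving aside every other source of loss, such as samples not given:

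confirmed rate = true rate × (1 − f)

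It follows that

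confirmed relative risk = true relative risk × (1 − f1)/(1 − f0).

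The direction does not depend on the planning rates. The relative risk shrinks when f1 exceeds f0 and is unchanged when they are equal. On the absolute scale, with 16% and 21% as true rates, the difference shrinks when 0.21 × f1 > 0.16 × f0, that is when f1 > 0.76 × f0.

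**Illustrations.** The middle columns take 16% and 21% as true rates and show what would be recorded. The last column keeps them as confirmed rates, as the article words them, and divides by (1 − f) to show the true rates needed to reach them.

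| f0, f1 (assumed) | Recorded if truth is 16% v 21% | Difference (points) | Odds ratio | Truth needed to record 16% v 21% |
|---|---|---|---|---|
| 5%, 5% | 15.2 v 19.95 | 4.75 | 1.39 | 16.8 v 22.1 (5.3 points) |
| 2%, 5% | 15.7 v 19.95 | 4.3 | 1.34 | 16.3 v 22.1 (5.8 points) |
| 5%, 10% | 15.2 v 18.9 | 3.7 | 1.30 | 16.8 v 23.3 (6.5 points) |
| 5%, 15% | 15.2 v 17.85 | 2.65 | 1.21 | 16.8 v 24.7 (7.9 points) |

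Example for 5% and 10%: 0.16 × 0.95 = 0.152 and 0.21 × 0.90 = 0.189, a difference of 0.037. In reverse, 0.16/0.95 = 0.168 and 0.21/0.90 = 0.233, a difference of 0.065.

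Two features bound the point. With equal shares of 5% the odds ratio, which is what the primary analysis compares, moves only from 1.40 to 1.39. To remove a true 5-point effect altogether with f0 = 0, f1 would have to reach 1 − 16/21 = 24%, which is an extreme case.

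I have not turned these scenarios into power. The article's power statement concerns the confirmed outcome, and the shares are assumptions.

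**The case against.** The strongest reply has five parts.

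*The article is a condensation.* It nowhere says that a woman on NRT with raised cotinine is a smoker. The rule for continuing smokers covers women who do not complete verification, which is a different group. The items of the structured interview are not listed, so NRT use may already be asked. This is fair as to what else may exist. It does not remove the point, because the article fixes the marker, the threshold and who is sampled. An abstainer above 8 μg/L is not cotinine-confirmed under that definition. If current use is not recorded at the time, no later analysis plan can recover it.

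*The planning rates are already confirmed rates.* This stands. A reader might take the table as showing that the planned 5 points will be eroded to 3.7 or 2.65. The documents do not support that, since 16% and 21% may already allow for some loss at verification.

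*The shares have no support.* This also stands. The guidelines reserve NRT for women otherwise unable to quit, Table 2 measures its offer and not its use, and only use recent enough to affect a postpartum sample counts. A reader might infer that every woman who quit with NRT is misclassified. The text does not support that either.

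*The self-report outcome covers it.* Only in part. It avoids this error by dropping verification for everyone, so a gap between the two outcomes could reflect either NRT use or misreporting.

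*Accepting self-report from NRT users in the primary outcome could be worse.* Women who both smoke and use NRT would bypass verification, more of them after the intervention if use rises, and the bias could then favour MOHMQuit. This stands, and it is why the primary definition should be left alone.

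**Conclusion.** The point holds as a conditional one. As fixed in the article, the primary outcome cannot separate smoking from NRT use at the time of sampling, and the trial aims to increase care that includes NRT. If use near the sample rises after the intervention, the primary effect is attenuated toward the null. The error described here would not create a false claim of benefit.

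The documents do not support the flat statement that the primary outcome is biased against MOHMQuit. That needs a rise in NRT use at sampling, on which they give no information. The size is unknown: negligible on the odds ratio scale if use is equal in the two phases, and larger only if use differs clearly between them.

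The conclusion rests on one fact that the article does not state, namely that NRT raises cotinine, which is basic pharmacology. The same would apply to any other nicotine product, but e-cigarettes are not mentioned in the article and nothing there says that MOHMQuit changes their use.

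**What to change.** 1. Add a question on current use of NRT and other nicotine products to the telephone interview and to the saliva collection form, unless it is already there.
2. Keep the cotinine-confirmed primary definition unchanged.
3. Prespecify a sensitivity analysis in which self-reported abstainers above the cut-point who report current nicotine-product use and no smoking are counted as abstinent, fitted with the primary model.
4. Report nicotine-product use among self-reported abstainers by phase, so that readers can see whether the condition for attenuation is met.

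The cost is one or two items and one further model. The sensitivity analysis rests on self-report for the women it reclassifies, so it should be read as a bound beside the primary result and not as a replacement for it. For women already sampled before the item is added, current use will be unknown, so the item should go in as early as possible and the date of the change should be reported.

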### Analysis to examine the mechanisms of action (aim 8)

To examine the causal linkages between the strategies, mediators, moderators and implementation outcomes structural equation modelling will be undertaken using data from clinician surveys collected pre-training and 6 months post-training. The primary outcome will be the change in the composite score of self-reported provision of SCS between pre-training and 6 months post-training. We will use structural equation modelling to estimate the direct and indirect effects of each of the intervention strategies (as articulated in Additional file 1) mediated by changes in the mediator scores listed in Table 2. A detailed statistical analysis plan will be developed.

### Sample size

The trial aims to recruit 4320 pregnant women who smoke over the 32 months of data collection across the nine sites.

NSW Health data indicate there were over 2000 women smoking in the first half of pregnancy in the participating sites in 2018. Assuming that at each of the 9 sites on average 40 participants will consent every 2 months, the total sample size available will be 9 × 40 × 12 = 4320. Using a significance level of 5% and assuming an intra cluster correlation (ICC) of 0.02 and a cluster autocorrelation of 0.7, the primary analysis will have more than 80% power to detect an increase in 7-day point prevalence abstinence of 5% from a baseline prevalence of 16% (i.e. intervention 21% vs control 16%). This conservative estimate is based on the effectiveness of antenatal psychosocial smoking cessation interventions in the latest Cochrane review (RR 1.44, 95%CI 1.19–1.73) [17].

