**Methods:**

A stepped-wedge cluster-randomised design will be used. Implementation of MOHMQuit will include reinforcing leadership investment in SCS as a clinical priority, strengthening maternity care clinicians’ knowledge, skills, confidence and attitudes towards the provision of SCS, and clinicians’ documentation of guideline-recommended SCS provided during antenatal care. Approximately, 4000 women who report smoking during pregnancy will be recruited across nine sites. The intervention and its implementation will be evaluated using a mixed methods approach. The primary outcome will be 7-day point prevalence abstinence at the end of pregnancy, among pregnant smokers, verified by salivary cotinine testing. Continuous data collection from electronic medical records and telephone interviews with postpartum women will occur throughout 32 months of the trial to assess changes in cessation rates reported by women, and SCS documented by clinicians and reported by women. Data collection to assess changes in clinicians’ knowledge, skills, confidence and attitudes will occur prior to and immediately after the intervention at each site, and again 6 months later. Questionnaires at 3 months following the intervention, and semi-structured interviews at 6 months with maternity service leaders will explore leaders’ perceptions of acceptability, adoption, appropriateness, feasibility, adaptations and fidelity of delivery of the MOHMQuit intervention. Structural equation modelling will examine causal linkages between the strategies, mediators and outcomes. Cost-effectiveness analyses will also be undertaken.

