### Stepped-wedge cluster-randomised controlled trial design

The MOHMQuit trial uses a stepped-wedge cluster-randomised controlled trial design with random allocation of services to the intervention order [48–50]. All services begin as part of the control condition and are randomised to transition from the baseline condition (standard care) to the intervention at specific intervals or ‘steps’ [48, 49]. Each step will occur at two monthly intervals (Fig. 2). There is a 3-month intervention period during which the intervention is provided and embedded in the service, and a 5-month ‘washout period’ to allow time for women receiving care in the baseline period to complete their pregnancies, thus eliminating contamination between baseline and follow-up periods (Fig. 2). The trial was originally planned to run over 36 months at eight sites. However, due to the impacts of COVID-19 and some redesign work being completed in *e*Maternity, initiation of data collection and provision of the intervention was delayed. To compensate for the reduced time available for data collection, an additional site was added (site six in Fig. 2), and the timing of providing the intervention at the final site brought forward. This ensured the study was still adequately powered.

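### The stated power of more than 80% does not follow from the stated design; with the 8-month gap and a time effect it is far lower, about 25% to 38% in the base case

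*Protocol article*

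**What the plan says.** The Sample size section multiplies 9 sites by 40 women per two months by 12 periods to reach 4320 women. With a 5% significance level, an ICC of 0.02 and a cluster autocorrelation of 0.7, it states that "the primary analysis will have more than 80% power to detect an increase in 7-day point prevalence abstinence of 5" percentage points, that is 21% against 16%.

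The section on the stepped-wedge design sets steps two months apart and then says: "There is a 3-month intervention period during which the intervention is provided and embedded in the service". A 5-month washout follows, so that women cared for in the baseline period can finish their pregnancies. After delays, a ninth site was added and the final site's start was brought forward. Of this change the article says: "This ensured the study was still adequately powered".

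The primary-outcome row of Table 2 specifies a logistic mixed model in which "a fixed effect for time will be included to adjust for any secular trends in the outcome", with random effects for site and for time within site.

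**The concern.** A stepped-wedge trial that adjusts for time learns mainly from calendar periods in which some sites are in baseline while others are in follow-up. Here each site leaves the comparison for 3 + 5 = 8 months, four times the step length. When the first site enters follow-up, most of the others have already left baseline. In the remaining calendar periods all the data come from one condition, so intervention and time are hard to separate. A power figure above 80% looked implausible for that layout.

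The stake is how a null result would be read. The primary hypothesis is a 5-point gain, and the Discussion says the evidence will inform decisions on at-scale implementation. A non-significant result set against a claim of more than 80% power would be taken as good evidence that no such gain exists. At the power computed below, a true 5-point gain would be missed more often than it is found.

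**Working it through.** **Inputs from the article.** 9 sites; 32 months = 16 two-month periods; a gap of 8 months = 4 periods per site; 40 women per site-period; ICC 0.02; cluster autocorrelation 0.7; 16% against 21%; fixed time effect; random effects for site and time within site.

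**Assumptions.** One site per two-month step; two-sided 5% test; time either categorical or linear. The article fixes none of these in the text shown.

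**The sample size reproduces.** 16 − 4 = 12 periods per site, and 9 × 40 × 12 = 4320. The multiplier of 12 is exactly what remains once the 8-month window is left out, which supports treating the gap as missing cells.

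**Overlap.** In the first follow-up period of the first site, four sites are still in baseline. The following periods hold 3 baseline and 2 follow-up sites, then 2 and 3, then 1 and 4. That is 4 calendar periods and 5 + 5 + 5 + 5 = 20 of 9 × 12 = 108 site-periods.

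**Variance components** (generalised least squares on site-period means, risk-difference scale, mean prevalence 0.185):
- total: 0.185 × 0.815 = 0.1508
- site: 0.02 × 0.7 × 0.1508 = 0.00211
- site by period: 0.02 × 0.3 × 0.1508 = 0.00090
- sampling of a mean of 40: 0.98 × 0.1508 / 40 = 0.00369

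**Power** = Φ(0.05/SE − 1.960). **Detectable difference** at 80% power = (1.960 + 0.842) × SE = 2.802 × SE. Reaching 80% for 5 points would need SE = 0.05/2.802 = 0.0178.

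- Categorical time: SE 0.0386. 0.05/0.0386 = 1.295; Φ(−0.665) = 25%. Detectable: 2.802 × 0.0386 = 10.8 points. The result is the same for every first-step date tried.
- Linear time: SE 0.0305 to 0.0324 depending on the first step. Power is 34% to 38%; detectable 8.5 to 9.1 points.
- Simulated binary outcomes (4000 runs) with the first step after two baseline periods: 24.5% (categorical) and 33.0% (linear).

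**Variants that keep the gap and a time effect, at 40 women per site-period:**
- final site brought forward: 18% to 22% categorical, 31% to 36% linear
- time in 12-month blocks: up to 41%
- one-sided test: 36% categorical, 46% to 50% linear, up to 54% with 12-month blocks
- ICC set to 0, two-sided: 37% categorical, about 53% to 57% linear
- best of 20,000 randomly drawn schedules, categorical, two-sided: 46%

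**Variants that depart from the design or the model** (first step after two baseline periods, two-sided unless noted):
- gap ignored, 12 periods: 60% categorical, 61% linear
- gap ignored, 16 periods (9 × 40 × 16 = 5760 women): 65% categorical, 71% linear (73% linear if the first step comes one period earlier)
- gap ignored, 16 periods, linear time, one-sided: 81%, or 85% with the variance taken at 16%
- gap kept, no time effect: 94% (91% to 94% over first-step dates)

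**The case against.** The strongest reply is that the exact schedule is in Fig. 2, which is not shown, and that the article states neither the coding of time nor whether the test is one- or two-sided. It also confirms an irregularity, since one site was added and another moved forward. This part stands: no single power value can be asserted from the text, and the overlap count of 20 site-periods depends on one site per step. It does not rescue the claim. Moving the final site forward lowers power under categorical time, and even a free choice of schedule stays far below 80%.

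A second reply is that the planned model is logistic, while the check is on the risk-difference scale. The scale should change the figures only modestly, and the simulation of binary outcomes agrees with the formula. A small-sample correction for nine clusters would push power down further.

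A third reply is that such detail belongs in the analysis plan. The coding of time may. The power figure, however, is stated in the article as a result, and the article's own inputs do not produce it.

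Two stronger readings are tempting and are not supported. A reader might infer that the authors must have left the time effect out of their calculation. The article does not say how power was computed, and a one-sided test with linear time and the gap ignored also passes 80%. A reader might also infer that the loss can be recovered at no cost by keeping women from the gap under one transition indicator. That assumes a constant effect over eight months in which the article describes the intervention being phased in. At 40 per period it would also use 5760 − 4320 = 1440 women beyond the stated target.

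**Conclusion.** The claim of more than 80% power is wrong as written, and so is the statement that the redesign kept the trial adequately powered. With one site per two-month step and a two-sided 5% test, power for 16% against 21% is about 25% with categorical time and 34% to 38% with linear time. Over plausible schedules, time codings and sidedness it is roughly 20% to 55%. At the stated recruitment, no variant tried that keeps both the 8-month gap and a time effect reaches 80%. With a two-sided test, ignoring the gap gives about 60% to 73%, and dropping the time effect, contrary to Table 2, gives 91% to 94%.

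The direction is secure. The exact figure is not, because it depends on Fig. 2 and on choices the article leaves open. The finding concerns the stated power and what a null result can bear. It does not show that the planned analysis is biased.

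**What to change.** Recompute power from the actual exposure matrix in Fig. 2. Treat the 8-month window at each site as missing cells, include the fixed time effect of Table 2, and state the coding of time and the sidedness used. Then replace the power claim in the Sample size section, and the adequacy statement in the section on the stepped-wedge design, with the resulting power for 5 points and the difference detectable with 80% power. Say alongside it that a non-significant result will be judged by its confidence interval and not taken as evidence against a 5-point gain.

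The work is one calculation and two edited sentences. The downside is a less favourable power figure in print.
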